### **Stage Two**

To enable availability of research findings in a timely manner to inform the national screening programme the number of practices was increased to 14 practices (seven implementation

practices and seven comparison practices). This will achieve the primary aim of testing the “non-inferiority hypothesis” in 12 months. Please see the “Sample size” section for further detail.

The same methods used above in stage 1 will be used to randomly select an additional three practices for the implementation arm from the remaining eligible practices. The random selection will be stratified by practice size and rurality. Within each of the small-rural and small-urban practices, one practice will be randomly selected (n=2). The third practice will be randomly selected from the large practices. This gives a total of seven practices in the implementation arm.

An additional three practices with similar characteristics to the implementation practices will be asked for permission to retrospectively access data from records obtained through clinical care for comparison to the implementation practices.

At the completion of Year 1 the study will have reached the number of participants needed for analysis. In agreement with the Ministry of Health we will offer HPV self-testing in Year 2 to comparison clinics for up to one year or until the new national screening programme starts. Women will still be asked to complete a consent form as this will be part of the research. The research team will use canSCREEN as the database for this group to ensure clinical safety.

### **Implementation practice training**

Key clinician champions identified by Mahitahi will undertake a clinical update and train the trainers programme. This will be provided by expert members of the research team. These key clinician champions will then undertake to visit each implementation practice and train clinicians and kaiāwhina and community workers. These trainers will be supported by the experts in the research team. The training will include comprehensive patient information and teaching aids, which will be available in Te Reo and English with easy to follow flow charts and diagrams. Materials have been developed in consultation with the community during our previous study in this rohe, and are being re-visited for this study. Consent and information sheets are in the appendix.

One-to-two hour workshops will be held in each practice or suitable venue involving:

- Presentations on HPV, its role in cervical cancer, prevention, colposcopy
- Role-playing of real life scenarios e.g. how to get proper informed consent, how to teach women to take their own vaginal swab
- Question and answer sessions.
- The practical logistics of labelling swabs, assigning study number, transporting swabs and organising result giving

The practices will co-ordinate the testing, community outreach, results and follow up.

### **Taking the swab**

Women will be given the participant information and consent form and if they agree they will be consented. This will include consent for copy of HPV results, (and if colposcopy is required, copies of histology results) to be sent to the senior researchers as well as the ordering health practitioner. Consented women will receive verbal, written and /or pictorial instructions from a doctor, nurse or kaiāwhina (community health worker) about how to perform the HPV self-test, a self-collected vaginal sample.

Women will self-collect a vaginal sample using a nylon-flocked swab (Copan Floqswab, Copan, USA). The instructions will detail how to insert the swab into the vagina and place it into a collection container.

---

 We may also translate materials into other languages if required by the practices, for example Samoan and/or Tongan

Women are at the centre of this study and we are led by their preference of where the swab will be taken. Most swabs will be taken by women in the practice, some opportunistically when the woman attends for another reason. If women feel uncomfortable about administering the swab themselves it can be taken by the clinician. Some women will do the test in their homes during a trained kaiāwhina visit and the swab returned to the practice by the kaiāwhina for routine lab collection. For some, this may involve leaving the swab in the letterbox for the kaiāwhina to pick up. While we will not encourage mailing the swab, this will be an option if required by women. All lab request forms must have a clinician's name on it as the clinician is responsible for giving HPV results (not the kaiāwhina).

### **Labelling**

Every practice has labelling machines and this will be done the same way as for other tests. Kaiāwhina who are making home or marae visits can take pre-printed labels with them if they know the person they are recruiting to the study. However, they may also be able to recruit other women while visiting a home or community centre if that woman is registered with the practice and due or overdue a smear. In these instances the kaiāwhina can manually write labels for the test samples and add the NHI on return to the practice. The test sample will be labelled as other tests are routinely done with the name, date of birth and unique NHI number of the woman being tested. When informed consent is obtained from the woman she will be asked how she wishes to obtain the results and the clinician/ kaiāwhina will document this. Women will also be asked if they can be contacted at a later date by one of our qualitative researchers and if so, contact details will be written on the consent form.

### **Transport**

Specimens will be transported at room temperature to Southern Community Laboratories (SCL) in Dunedin who are contracted to perform the testing.

### **Laboratory Test and Process**

HPV genotyping will be carried out using PCR platforms to distinguish HPV-16 and HPV-18 from other high-risk types and from negative samples. All main New Zealand laboratories have the capability to perform the recommended HPV PCR testing. The use for this study on dry vaginal swabs has been validated in international published studies and the contracted lab Southern Community Laboratories will agree to do this 'off-license' testing as part of this study.

### **Results**

Results of the HPV assay test will be sent electronically encrypted (as other routine results) to the ordering primary care clinician at the primary care health practice and entered into a recall database. The database will enable recall and reminders to be sent to the woman.

### **Giving results**

The primary care clinician will give the results to the woman by the method she opts for at the time informed consent is obtained. This might be by text if negative or by phone or in person at the practice. If the test is 'unsatisfactory' or 'invalid' for testing the lab will request another sample from the woman taken ideally within 6-12 weeks. Invalid results are very unusual with HPV testing.

### **HPV negative result**

The woman will be informed of the result and advised that she will not need another test for at least five years. This can be an HPV self-swab as the NSU will implement HPV testing in 2023 .

### **HPV high-risk positive result**

Women may have results that are positive for HPV 16, 18, or other high-risk HPV types. Results will be given to these women in person, face-to-face (kanohi-ki-te-kanohi) or by telephone (depending on

participants chosen method) in a sensitive and appropriate way. Women may choose to have whānau or friends to support them when receiving the results. It will be emphasised by the clinician that having an HPV high-risk positive results DOES NOT mean that the woman has cancer – this is very unlikely - but it may indicate that there are pre-cancer changes on the cervix. These changes can be identified and treated BEFORE they develop into cancer. Women will receive as much information as they need about the referral process to colposcopy and the colposcopy process itself using NSU information already available as well as verbal information from the trained primary care clinician. Women and whānau can be navigated through these steps. Women will be supported to colposcopy through existing support networks where available.

### **canSCREEN database**

The new NCSP has funding to switch to a new primary HPV screening register in 2023. Until then, the NCSP cannot automatically register HPV results on the NSU database, as there will be no accompanying cytology. The ordering health practitioner and the research team are therefore responsible to follow up on these results.

For this project we will adapt the canSCREEN database to perform the equivalent function as the NCSP for women who have an HPV test. The canSCREEN database is a fully developed cancer screening registry platform developed and operated by VCS Foundation in Australia which will be modified to meet the needs of Te Tai Tokerau/Northland.

The canSCREEN database will hold information about HPV testing and follow-up: practice attended, HPV test results; cytology triage (for HPV-other); colposcopy referral, attendance and histology; and treatment/ discharge/ 12-month follow-up. The canSCREEN database will function as a safety net, supporting healthcare staff to identify and contact women who have not presented for follow-up tests and/ or colposcopy appointments. The canSCREEN database will also hold information relevant to monitoring eligibility and safety such as name, address and date of birth.

We anticipate at the conclusion of the project, data contained within the canSCREEN database will be migrated to the NCSP to support women's ongoing participation in cervical screening, unless individual women opt-out of this process.

The database will be modified to adapt to the needs of Northland health care providers and women in terms of how unique identification and inputs and outputs are managed within the screening pathways eg mobile interfaces, off and online, reminders and work lists can be paper based, sent by email, or SMS. Business analysts and developers will work closely with the researchers and clinicians to map the clinical pathways and requirements into the business rules of a Northland module of the register. Depending on travel restrictions and allowances between Melbourne and New Zealand, this will either be in person (preferred option) or by Zoom/Teams.

The platform is highly secure and supports role based access by which healthcare workers and research staff can only access agreed data and functions. Data are held securely on the Azure platform and hosted by VCS. Access is only available by named investigators, clinical staff and digital support staff. All VCS staff are required to comply with strict confidentiality requirements including signing annual declarations to comply with confidentiality requests.

### **Triage (see Figure 2.)**

If a woman has a positive high-risk HPV result then it is the responsibility of the ordering health practitioner to organise the referral for colposcopy and the senior co-ordinating researcher or project manager will also liaise with the health practitioner to ensure clinical safety. A standardised

pro-forma letter will be sent to the colposcopy practice with usual clinical referral information stating that the woman is part of this study and why cytology is not available nor NSU registration. See below for study process at colposcopy.

Triage for colposcopy after using HPV primary screening has not been tested in Aotearoa. What is recognised is that referring all HPV positive women straight to colposcopy would increase the numbers of unnecessary colposcopies dramatically and potentially overwhelm the secondary service. To mitigate this and because the HPV 'other' types are much less likely to cause pre-cancer changes and most women will actually clear the virus in time, a triage system will use HPV testing combined with cervical cytology. The Te Ara Waiora Project working with the NDHB colposcopy team and the MOH expertise group will trial the preferred system of triage. If an HPV self-test is positive for types 16 or 18 (causing 70% of cervical cancer) the woman will be referred to colposcopy. If the test is positive for HPV 'other' types the woman will be called back for a cervical smear for cytology to triage for whether she needs colposcopy then, or can be re-tested for the HPV one year later. If the woman declines cytology after an HPV 'other' test she can have a repeat HPV test at 9 months but particularly if she is under or never screened and declines to have cytology she may be referred straight to colposcopy. If the woman does not have cytology after three months of her positive HPV 'other' result, she should be referred to coloposcopy. This will be discussed with the colposcopy team and allows for the pathway to be woman centred and more flexible.

## Figure 2: Triage

**Figure 2. Te Ara Waiora – Implementing HPV primary testing in Aotearoa New Zealand: triage and referral pathways following an HPV test.**

[figure not shown]

 Women who are under-screened or never screened and have a positive HPV 'other' high risk result but decline cytology may be referred for colposcopy or return for another HPV test in 9 months.

 Women who are immunosuppressed and have a positive HPV 'other' result should be offered cytology AND referred for colposcopy.

 Those who have a positive HPV 'other' result on their second test in 12 months AND who are over 50 should be referred to colposcopy. See supplementary Figure for detail.

**Supplemental Figure: Triage and referral pathways for women who have two HPV ‘other’ high-risk test results 12 months apart.**

[figure not shown]

**Figure 4: Triage for women with previous abnormality, not undertaking test of cure, not back to 3 yearly cytology and/or lost to follow up**

[figure not shown]

**Women with recent treated abnormality who have not yet completed TOC are excluded from HPV self-test study**  
 [HPV and cytology annually until both negative in 2 consecutive years] as per current NCSP guidelines

## **Barriers and facilitators to the triage system for HPV positive women**

There are unique questions about triaging that we will answer through qualitative data collection especially about women who receive a positive HPV 'other' result upon an HPV self-test who will be triaged to cytology (see Figure 2). Wāhine from the following groups will be included:

- Up to 10 women who test HPV HR16 or 18 and go straight to colposcopy
- Up to 10 women who test HPV HRother and go through the triage system
- Up to 10 women who test HPV HRother and choose to go straight to colposcopy

Interviews will take place at a time and location of the participants choosing. Although the research is not restricted to Māori participants, we anticipate that many will be Māori (given the population of Te Tai Tokerau). The researchers will draw on Kaupapa Māori Research practices, which have also been described as Community-up research practices, whereby whakawhanaunga (developing relationships), participant safety, and research accountability are paramount.

Questions include, from the women's perspectives: how does the triaging work? what barriers and facilitators exist on this new pathway? This is especially important for never/under-screened women who find current screening (cervical cytology) unacceptable. We need to ensure that triaging does not create barriers to diagnostic care.

Perspectives of key stakeholders such as practice managers, doctors, nurses, kaiāwhina and PHE representatives on experiences of implementing HPV self-testing for primary care will provide critical knowledge on barriers and facilitators to implementation.

## **Enablers for 25 year olds to participate in screening**

At the request of the NSU, we will also be focussing on 24/25 year old wāhine to explore what would encourage them to participate in screening, for example free screening, mail-out, self-sampling, offer of free HPV vaccination. We will address this with action research including qualitative focus groups. It is important to capture the voices of these wāhine. Multiple focus groups across different ethnicities, especially wāhine Māori and Pacific women, sexualities and abilities would strengthen this kaupapa. Our proposed action research methodology component added to the existing study will involve kaumātua, kuia and different locations including Marae and sports venues. Action research will enable 24/25 year olds to develop their research skills and will underpin the research with different experiences and worldviews of wāhine in this age group. In addition to hearing about views of free screening/mail out/self-sampling/offer of free vaccination we will also trial other methods such as direct approach to women from NGOs, kaiāwhina and primary care practices.

## **Support needed for participants invited via a population based register and not enrolled in primary care to participate in screening**

The NSU have also asked us to hear from whānau who are not enrolled in primary care about support needed to participate in screening. Our community partners have told us there is difficulty with transient addresses in identifying these wāhine but they can often be found with the connections, expertise and trust of kaiāwhina and kaumātua. We will aim to have focus groups or interviews with up to 20 wāhine and 10 kaiāwhina/kaumātua community workers/other primary care staff. The team is very experienced in community research and able to connect with those wāhine who the system is not readily engaging with.

### **Training requirements for staff who are not registered sample takers but could be trained to deliver swabs to those wishing to take a self-sample outside of the medical clinic setting**

We will be delivering training to kaiāwhina, health coaches and health improvement practitioners for the study. We will interview these staff about training requirements and how to strengthen these roles within the system of screening, which may include micro-credentialling. Our study partners Mahitahi alerted us to the gap in knowledge around support to screening services. This includes support in accessing the HPV self-test but also the cost of supporting women to colposcopy. These contracts are held by Māori health providers in Te Tai Tokerau. We propose interviews with those who provide support to screen services to find out facilitators and inhibitors to providing this service.

### **Level of knowledge and educational needs for providers**

This is an important issue, for example gaps in knowledge about how to explain screening and HPV testing to women. We will hear from a wide range of providers, with steering committee, community and PHE input and qualitative interviews. These will highlight what providers need to know to help women navigate the screening system and understand their screening results.

### **What support do women need to get their results? After positive test, after negative test?**

Our previous qualitative research has highlighted the support women need to get their results and support to colposcopy. The qualitative component of our existing study answers unique questions about triaging through qualitative data collection especially about women who receive a positive HPV 'other' result upon an HPV self-test who will be triaged to cytology. We can extend these interviews to include women who have negative tests. Perspectives of key stakeholders such as practice managers, doctors, nurses, kaiāwhina and PHE representatives on experiences of implementing HPV self-testing for primary care will provide critical knowledge on barriers and facilitators to implementation.

### **What we need to do to ensure women are followed up for positive HPV tests, including the level of support needed**

- Rates of follow up
- Colposcopy and follow-up cytology
- How to improve liaison between labs/primary care/colposcopy services

Our implementation study will answer these questions. We will identify questions such as who is responsible for follow-up, what is working well and why, as well as challenges to communication and information sharing. We will explore who makes colposcopy appointments and test ideas for different ways of streamlining the screening system in ways that women are kept safe. Our goal is to inform a seamless system by sharing data and regular meetings.

Data will be analysed thematically, with participants' talk grouped into themes and subthemes. Barriers and facilitators of timely access to the appropriate care will be identified.

### **Colposcopy**

Based on overseas figures we would expect 2.5% of women to need direct referral to colposcopy with a positive 16/18 test, with any woman with CIN 2+ disease requiring treatment. Colposcopies will be done through the Northland DHB Gynaecology outpatients as agreed with the Chief Medical Officer ([name]) and the Colposcopy team at Northland DHB (lead colposcopist [name] and [name], lead nurse) who all support this project.

At colposcopy the woman will automatically be registered on NSU database. A cytological sample should be taken. Colposcopy will be performed in the routine fashion and documentation of colposcopy will be recorded on gynae - plus database. In view of the fact that cytology will not be available at the time of colposcopy further reducing the sensitivity of colposcopy the threshold for

biopsy should be low. In the case of an abnormal transformation zone (TZ) of cervix, it is recommended that more than 1 biopsy is taken and if the TZ is normal, a random biopsy should be taken to confirm normal histology. If the TZ is not visible, the patient will be reviewed in the light of the cytology result, HPV type and other clinical details.

### **Funding for HPV tests and colposcopies**

Women will pay the usual fee at their general practice for a screening consult and the HPV test will not incur any additional cost. Mahitahi will fund the HPV laboratory tests for the first stage of the study and the second stage tests will be funded by the MOH. There will be no cost to the woman for the swab or the lab test. The study will fund all colposcopies. Referral will be made straight away if the test is positive for any high risk HPV and should be seen within 20 working days. We have consulted with the colposcopy team at NDHB about the increase in colposcopies expected for the duration of the study and they have agreed to this potential increase in colposcopies and are supportive of the study.

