### **Funding for cytology required for HPV Other high risk**

The MOH triage process requires cytology for women with HPV Other high risk results. This will be paid for by the study.

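### The funding section refers every high-risk HPV positive woman to colposcopy at once, which contradicts the cytology-first triage for HPV 'other'

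*Protocol*

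**What the plan says.** Two places in the Protocol give a rule for who goes to colposcopy after a positive HPV test.

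- **Funding for HPV tests and colposcopies:** "Referral will be made straight away if the test is positive for any high risk HPV and should be seen within 20 working days".
- **Triage:** "If an HPV self-test is positive for types 16 or 18 (causing 70% of cervical cancer) the woman will be referred to colposcopy". For a test positive for HPV 'other', "types the woman will be called back for a cervical smear for cytology to triage for whether she needs colposcopy then"; otherwise she is re-tested for HPV a year later. The same section gives the reason: "referring all HPV positive women straight to colposcopy would increase the numbers of unnecessary colposcopies dramatically".

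Three further sections bear on the choice between them.

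- **HPV high-risk positive result** sets the scope of the term: "Women may have results that are positive for HPV 16, 18, or other high-risk HPV types".
- **Funding for cytology required for HPV Other high risk**, which directly follows the funding section, says: "The MOH triage process requires cytology for women with HPV Other high risk results".
- **Colposcopy** gives the only planning figure: "we would expect 2.5% of women to need direct referral to colposcopy with a positive 16/18 test".

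**The concern.** The trigger in the funding section is any high-risk type. Because the protocol includes the 'other' types under that term, the sentence orders immediate referral for women whom the Triage section sends to cytology first. Both are current text and both are instructions about follow-up of HPV positive women.

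The sentence carries a trigger and a time limit, so it reads as a working rule even though it sits under a funding heading. If a practice applied it, women with 'other' types would reach colposcopy before the cytology meant to decide whether they need it. That would add procedures of the kind the protocol itself calls unnecessary. It would bypass the triage pathway that the study sets out to trial. It would also change the group in which secondary outcome 7 (high-grade lesions among women attending colposcopy) is measured.

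**Working it through.** **Step 1. Does the funding sentence cover HPV 'other'?** Yes. The results section lists 16, 18 and the other types together as high-risk results, and the cytology funding section has 'Other high risk' in its heading. Nothing in the funding sentence narrows the term.

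**Step 2. Which rule is intended?** Setting the remaining text beside the two rules:

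| Place in Protocol | Content | Fits immediate referral of all positives? |
|---|---|---|
| Triage | 16/18 to colposcopy, 'other' to cytology, with the reason stated | No |
| Funding for cytology | Cytology required for 'other' | No |
| Figure 2, footnote 2 | Immunosuppressed women with 'other': cytology and referral | No, the exception would be redundant |
| Figure 2, footnote 3 | Women over 50 with a second 'other' result at 12 months: referral | No, the exception would be redundant |
| Barriers and facilitators to the triage system | One interview group is "Up to 10 women who test HPV HRother and go through the triage system"; a separate group chooses direct colposcopy | No, direct referral is not the default |
| Secondary outcomes 4 and 5 | 'Other' women followed to cytology, then to a one-year HPV test if cytology is negative or mild | No |

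Every entry points to cytology first. The funding sentence is the one that is wrong.

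**Step 3. What would literal use add?** The input is the 2.5% expected direct referral for 16/18 (Colposcopy section), taken here as a share of women tested.

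- Plan's figure: 0.025 × 1000 = 25 direct referrals per 1000 tests.
- Each percentage point of 'other'-only positivity: 0.01 × 1000 = 10 further immediate referrals per 1000 tests.
- With 'other'-only positivity of p percent, immediate referrals per 1000 tests are 25 + 10p under the funding sentence and 25 under the 16/18 rule.

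For scale, take the roughly 2800 women in the implementation arm, the assumed 72.5% screening rate, and every screen being an HPV test. Then 2800 × 0.725 = 2030 tests. The 16/18 referrals are 2030 × 0.025 = about 51, and each point of 'other'-only positivity adds 2030 × 0.01 = about 20.

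The protocol gives neither the share positive for 'other' only nor the share of those with cytology that leads to colposcopy, so p cannot be filled in. The added figure is gross: some of these women would reach colposcopy later under triage anyway.

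**Step 4. What does not move?** The Sample size section uses a 72.5% screening rate, a 10% margin, 400 women per practice and an intra-cluster correlation of 0.01. None depends on triage. The primary outcome is whether a screen took place, which is settled before referral. Outcome 6 concerns women with 16/18, for whom both rules agree.

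**The case against.** The strongest reply is that this is one loose line in a funding section. The section headed Triage, with Figure 2, is the operative rule and gives its reason; the next section requires cytology for 'other'; practices are trained with flow charts; and the canSCREEN database is to hold cytology triage for these women. A reader of the whole protocol can recover the right rule, and an error here leads to over-referral rather than missed follow-up. All of that stands and limits the weight of the point. It does not make the sentence correct, and in the readable text this sentence alone says how soon a woman should be seen at colposcopy, so someone checking urgency will find it.

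Some stronger readings are tempting, and the documents do not support them.

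- *That the Colposcopy section restricts direct referral to 16/18.* It gives an expected share and does not say only. The rule rests on the Triage and cytology funding sections.
- *That the colposcopy load would rise by a stated multiple.* This needs an 'other' positivity that the protocol does not give.
- *That the two rules differ by a fixed number of weeks.* The 20 working days run to being seen. The three months in the Triage section is the point at which a woman without cytology is referred. The two cannot be subtracted.
- *That outcomes 4 and 5 would be lost.* Referral does not preclude cytology, since a sample should also be taken at colposcopy. These outcomes serve here as evidence of intent.
- *That the rules for women who decline cytology contradict each other.* The Triage section allows a repeat HPV test at 9 months and also says that a woman without cytology after three months should be referred. The first is an option, the second may be a backstop for non-attenders, the pathway is described as flexible, and the content of Figure 2 is not visible here. This is a question to ask, not an error shown.

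**Conclusion.** The funding sentence is wrong as written: it orders immediate colposcopy referral for all high-risk types, while the protocol's triage requires cytology first for HPV 'other'. This follows from the text alone and needs no assumption.

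The size, if the sentence were followed, is 10 extra immediate referrals per 1000 tests (gross) for each percentage point of 'other'-only positivity, against 25 per 1000 expected for 16/18. This takes the 2.5% as a share of women tested. Nothing shows that any practice would follow the funding sentence over the Triage section, so this is the consequence of literal use and not a forecast. The primary outcome, margin, sample size and outcome 6 are untouched. It should be corrected because it is a clinical instruction and the correction is small.

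**What to change.** In Funding for HPV tests and colposcopies, replace the sentence with wording such as: *Immediate referral applies where the result is HPV 16 or 18, or where the triage pathway (Triage section, Figure 2 and associated figures) indicates colposcopy; the 20-working-day limit for being seen then applies.*

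At the start of the Triage section, where the ordering practitioner is made responsible for organising referral after a high-risk result, add: *where indicated by the triage below*.

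Use a cross-reference and not a closed list of indications. A list naming abnormal cytology would be too broad, because outcome 5 sends women with mild dysplasia to a one-year HPV test. It could also leave out the separate Figure 4 pathway for women with a previous abnormality and the women who choose direct colposcopy.

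Put one query to the clinical and colposcopy teams: for a woman who declines cytology after an 'other' result, does the three-month referral or the 9-month repeat HPV test govern?

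The cost is one sentence, one phrase and one query, plus a check that the canSCREEN rules match when the clinical pathways are mapped, which is already planned. Design, outcomes and sample size do not change.
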